### Participants

#### Recruitment and consent of participants

This study will recruit healthcare staff and students from the University of Manchester (UoM) and Manchester University NHS Foundation Trust (MFT). Recruitment into this study will be advertised during routine lectures, posters, ‘word of mouth’, snowball recruitment (asking participants to recommend further people to participate), UoM and MFT Bulletins, social media feeds, and noticeboards [13]. Advertisements contain a quick response (QR) code directing the individual to a participant information sheet (PIS) and consent form. On completion, they will be individually contacted, and instructions will be given on how to proceed with the study. Consent will be confirmed upon attendance at the VR simulation laboratory in UoM or a simulation skills area in MFT. Withdrawal from enrolment into this study is possible at any time, without stating any reason, and without any detriment to the participant.

#### Inclusion and exclusion criteria

For this study, specific inclusion and exclusion criteria have been defined ahead of the recruitment start date, and documented in the ethics application. These are listed below:Inclusion criteria are as follows:Healthcare studentClinical experience neededHealthcare staffBased at MFT, or The UoMExclusion criteria are as follows:Not a healthcare studentNot a healthcare student—have no clinical experienceNot healthcare staff but working in the NHSNot based at MFT, or The UoM

### Description of the intervention

The educational tool is a stand-alone software package hosted entirely on a VR HMD. It has been developed by VREvo Ltd www.sentiraxr.com. It is designed to be used without direct supervision by a technician or educator and to teach the following learning outcomes, model of the long-running NTSP paediatric tracheostomy safety course:Recognise that paediatric tracheostomy emergencies require placement of oxygenation via the mouth and nose.Recall critical equipment required during a blocked tracheostomy emergency.Learn to follow the NTSP paediatric emergency tracheostomy algorithm and, in doing so, practice the following steps to solve the emergency:Approaching the child should include safety, stimulation, shouting for help, and oxygen.Give oxygen via an appropriate route.Remove external attachments from the tracheostomy tube, e.g., the speaking valve.Using a suction catheter, Determine if the tracheostomy is patent or blocked.Perform an emergency tube change and reassess patency after the change.If the emergency tube change does not restore the airway, give five rescue breaths at an appropriate point in the resuscitation, using a suitable device and entry point (mouth or stoma).Experience working through the algorithm with various external and internal pressures and stressors to mimic real-world use.

The software package takes around 20–35 min to complete and has four distinct activities within the virtual environment. These are detailed in Table 1:

Following recruitment and electronic consent process, the participants will attend the study site (MFT or The UoM). At this point, following confirmation of consent, demographic data and the pre-course knowledge test will be administered (Appendix 1). Following this, the individual will be required to manage a standardised simulated blocked paediatric tracheostomy, which will be recorded, and performance data will be logged. The participants will then be provided with the VR training loaded onto a Meta Quest 3 head-mounted display (HMD) which they will take for one week. The participants will be expected to use the application at least four times, but up to as many times as required until they feel they have learnt the content effectively. They will be required to record their use, and we will record how many times it has been used and for how long (Appendix 1).

During the study, the participants will have access to an email address to ask technical support questions and open virtual calls regularly during the week if they need verbal technical support. The participant will be able to get in-person technical support at the university if required. All technical support requests will be documented and reported (Appendix 1). At the end of the one-week study period, the participant must return the HMD to the VR laboratory or simulation area and undertake a second simulated assessment. The outcome measures in these simulated assessments are identical to those completed in the study from which we will be taking historical controls and will form the basis for statistical comparisons. This scenario will teach and assess the same principles as the first but differ in specific clinical situations. It will be followed by a de-brief for educational purposes, which will not form part of the assessment or be recorded. The participant will also complete the electronic post-course questionnaire with a repeat knowledge test (Appendix 1). Finally, an electronic knowledge retention test, identical to the previous knowledge tests, will be completed four weeks after the post-course questionnaire. A certificate of participation, including a £75.00 incentive voucher, will be delivered electronically upon completion of the retention test. The study flow is diagrammatically represented in Fig. 1.

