### Overall aim and research questions

The novel VR tracheostomy training package will be used as described in Table 1. By evaluating this novel VR training package, we aim to explore whether healthcare students can gain knowledge and skills relevant to managing paediatric tracheostomy emergencies using immersive technology in their homes. In addition to skill acquisition and knowledge, we aim to understand the usability of these devices in the remote setting and learn about the user's satisfaction levels and perception of realism by utilising the training package in a self-directed manner. The research questions are as follows:Is fully remote, unsupervised VR training non-inferior to traditional training?Do participants enjoy and feel they can learn from fully remote VR training?

**Table 1 Tab1:** Summary of the VR educational activity

Activity	Detail
**Onboarding (5 min)**	This 5-min experience guides the participant through using the controllers to interact with the environment and virtual objects and move around. It teaches the user how to perform specific interactions, such as suctioning the tracheostomy and speaking to the avatar in the simulation
**History taking (5–10 min)**	The user is expected to take a brief history from a simulated avatar of the patient’s mother as they have attended the emergency department due to a cough and fever. The user will be able to ask relevant questions verbally and be responded to by the avatar. The aim is to gather any information regarding when the tracheostomy was inserted, when the tracheostomy was last suctioned, any allergies the patient may have, and whether the patient has eaten before coming to the hospital. This is to determine whether the procedure can go forth
**Algorithm tutorial training (5–10 min)**	This is a guided tutorial that demonstrates and allows the user to practice using the emergency tracheostomy algorithm. It introduces the blue emergency box, algorithm card, and equipment required to complete the process of decannulating the child. There are no elements of stress in this scene; it is purely a learning space
**Algorithm simulation assessment (5–10 min)**	This section will expose the user to an emergency and require them to progress through the blocked tracheostomy algorithm Feedback is given to the user around time, including interventions they have completed and ones they missed The user can repeat the assessment or the tutorial to improve their time

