### Primary outcome—assessment of performance in simulation

The participants synthesised knowledge will be assessed before and after the intervention during a traditional simulation skills session. Both sessions will include a pre-brief, with the second session following up with a de-brief pedagogical methodology as per best standards in simulation design [14]. The simulation will have the same layout and equipment as the VR training tool. These sessions will be analysed on-site, and the following data will be taken:Overall success in task (measured as a binary ‘yes’ or ‘no’ outcome)Steps completed (all measured as a binary ‘yes’ or ‘no’ for each of the below individual steps marked a-g)Call for helpLook / listen / feelApply oxygen – faceApply oxygen – tracheostomyRemove any attachmentsAttempt suctionRemove tracheostomyTime to key interventions (measured in seconds for all individual steps below marked a-c)Apply oxygen to face and neckCall for helpCompletion of simulation

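### The on-site educational de-brief precedes the retention test and, as narrated, the repeat knowledge test, so the knowledge outcomes do not isolate remote VR training

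*Protocol article*

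**What the plan says.** The first research question (Overall aim and research questions) is: "Is fully remote, unsupervised VR training non-inferior to traditional training". The same section says the study will explore whether students can gain knowledge as well as skills by using the technology at home.

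Description of the intervention narrates the closing visit in this order:

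1. After one week, "the participant must return the HMD to the VR laboratory or simulation area and undertake a second simulated assessment".
2. Of the second scenario: "This scenario will teach and assess the same principles as the first but differ in specific clinical situations".
3. Of what follows it: "It will be followed by a de-brief for educational purposes, which will not form part of the assessment or be recorded".
4. Then: "The participant will also complete the electronic post-course questionnaire with a repeat knowledge test".
5. Last: "Finally, an electronic knowledge retention test, identical to the previous knowledge tests, will be completed four weeks after the post-course questionnaire".

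The primary outcome section confirms that the de-brief belongs to the second session: "Both sessions will include a pre-brief, with the second session following up with a de-brief pedagogical methodology". Knowledge gain and knowledge retention are listed as secondary outcomes in the Abstract, and the mean knowledge score is a named aggregate measure under Statistical calculations.

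**The concern.** The intervention under study is one week of unsupervised VR at home. The closing visit then adds two exposures that the protocol itself describes as teaching: the second scenario and the de-brief. If the knowledge tests come after these exposures, a higher score cannot be attributed to the headset alone.

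The likely direction favours VR, because further teaching on the same subject should raise scores or slow their decline. The analysis cannot undo this. Every participant has the de-brief, the only comparator is historical, and the de-brief is not recorded, so as described there would be nothing to adjust for. At stake is the statement, likely to be drawn from the knowledge results, that staff and students learned and retained the material from remote VR.

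**Working it through.** The document gives no figure to reproduce on this point. The check is one of sequence.

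**Retention test.** It is dated four weeks after the post-course questionnaire and is the last step. The second simulation and its de-brief belong to the closing visit. Nothing in the article allows the retention test to fall before them, so this order is certain.

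**Repeat knowledge test.** It is narrated directly after the de-brief. The linking word is *also*, which adds a task without ordering it, whereas the next sentence opens with *Finally*. Fig. 1 is not shown. No sentence places the repeat test before the de-brief. That it comes afterwards is therefore the natural reading, but not a stated rule.

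**Primary outcome.** Success, steps and times are taken during the simulation, and the de-brief follows it. The 30 s margin and the comparisons with historical data (total scenario time and time to key interventions) use these measures, so the de-brief cannot reach them.

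**What each order would measure after the VR week:**

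| Order at the closing visit | Exposures before the repeat test | Exposures before the retention test | Between the two tests |
|---|---|---|---|
| Simulation, de-brief, test (as narrated) | VR, simulation, de-brief | VR, simulation, de-brief | No further teaching stated |
| Simulation, test, de-brief | VR, simulation | VR, simulation, de-brief | De-brief |
| Test, simulation, de-brief | VR | VR, simulation, de-brief | Simulation and de-brief |

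The retention score includes the de-brief in every row. Knowledge gain includes it only in the first. The third row gives the cleanest knowledge gain, but it puts a knowledge test immediately before the simulation that supplies the primary outcome and so could prime it.

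**How sensitive a pre-post gain would be (an illustration, not an estimate).** Assume that 69 participants complete both tests, that the SD of change equals the SD of the score, that VR has no effect on knowledge, and that a two-sided 5% test is used. Let the de-brief alone shift the mean by d standard deviations. The probability of a significant gain is then approximately Φ(d × √69 − 1.96), with √69 = 8.307:

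- d = 0.1: Φ(0.831 − 1.96) = Φ(−1.129), about 13%
- d = 0.2: Φ(1.661 − 1.96) = Φ(−0.299), about 38%
- d = 0.3: Φ(2.492 − 1.96) = Φ(0.532), about 70%
- d = 0.5: Φ(4.153 − 1.96) = Φ(2.193), about 99%

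The values of d are assumed. The article supplies no de-brief effect and no SD for the knowledge score, and it names only descriptive statistics and means for this outcome. The range shows only that a modest contribution from another source could look like a VR effect.

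**The case against.** The strongest reply is that the article never says the repeat test follows the de-brief: *also* is not a sequence, and the flow diagram may settle the matter. This stands as far as it goes. It leaves the order of the repeat test as a natural reading, but it does not alter the position of the retention test.

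A second reply is that a de-brief is accepted simulation practice, and that any de-brief at the closing visit must precede a test four weeks later. This is fair. For retention the remedy is accurate description, not removal of the de-brief.

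A third is that moving the repeat test has costs of its own. In the narrated order the de-brief precedes both tests, so the change from post-test to retention test does not have it in between. Once the test is moved, it does. This also stands, and the downside must be named.

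Three stronger readings are tempting, and the document does not support them:

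- A reader might infer that the answer to the non-inferiority question is contaminated. It is not, because the measures named for that comparison are taken before the de-brief.
- A reader might infer that the knowledge tests do not measure VR learning at all. They do, but mixed with later exposures. Nor does the article state who leads the de-brief or what it covers; that it is delivered in person is inferred from the on-site session.
- A reader might count another departure from remote training in the sentence "The participant will be able to get in-person technical support at the university if required". That support is technical, not teaching, and requests are to be documented and reported. Excluding those who used it could remove participants who struggled with the headset and so flatter VR.

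**Conclusion.** The point holds in a limited form. The retention outcome certainly includes teaching given after the VR week, and so does knowledge gain on the natural reading of the article. Neither isolates remote, unsupervised VR, and the probable bias favours VR. It affects secondary outcomes only, but for every participant who attends the closing visit, and no concurrent group can remove it. The primary outcome and the time-based non-inferiority comparison stand untouched.

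The size of the bias cannot be derived from the document. Its direction rests on the assumption that the de-brief and the second scenario bear on the tested material. This is reasonable, because the scenario is said to teach the same principles as the first and the knowledge test is based on the course's learning outcomes. A change is worth making because it is specific and nearly free.

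**What to change.** State that the repeat knowledge test is completed at the closing visit after the second simulation and before the de-brief. This takes the de-brief out of knowledge gain without placing a test ahead of the primary outcome. Knowledge gain would still include the second scenario and should be reported as such.

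Describe the four-week result as retention after VR plus simulation and de-brief, not after VR alone. If visits have already taken place, report the order actually used and interpret both outcomes accordingly.

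The cost is the re-ordering of one electronic questionnaire within a visit and a sentence or two of interpretation. The downside is that the de-brief then lies between the post-test and the retention test and may mask forgetting, so the change between those two tests needs that caveat.

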**Fig. 1 Fig1:**
[figure not shown]
Study flow diagram demonstrating the process from recruitment to study completion

### Statistical calculations

Sample size calculations were performed by an MFT statistician (AR) to assess for non-inferiority of VR training compared to the current standard training. In the historical data set, the standard deviation for total scenario time after standard training was 70 s. The non-inferiority margin is assumed to be 30 s. Assuming the expected time to key specific interventions and completion of the scenario for the two groups are the same, the sample size is calculated so that the upper limit of the one-sided confidence interval for the mean difference in time (VR- standard) is below 30 s. A 97.5% one-sided confidence interval for non-inferiority translates to a 95% two-sided confidence interval, provided the upper limit is below 30 s. The calculation provided led to a proposed sample size of 69 participants. Descriptive statistics will be obtained from the pre and post course surveys and the assessment data. Secondly aggregate measures will be constructed for further analysis. Examples of aggregate measures include:Mean values for the simulation performance (primary outcome)Mean values for knowledge test score

The data will be compared to historical data from a course designed to teach the same learning outcomes. Specific measures for performance will be compared, including total scenario completion time and time to specific key interventions.

### Outcome measures

The process for assessing primary and secondary outcomes throughout the study period are outlined below. All of the data collection points are included in Appendix 1.

### Primary outcome—assessment of performance in simulation

The participants synthesised knowledge will be assessed before and after the intervention during a traditional simulation skills session. Both sessions will include a pre-brief, with the second session following up with a de-brief pedagogical methodology as per best standards in simulation design [14]. The simulation will have the same layout and equipment as the VR training tool. These sessions will be analysed on-site, and the following data will be taken:Overall success in task (measured as a binary ‘yes’ or ‘no’ outcome)Steps completed (all measured as a binary ‘yes’ or ‘no’ for each of the below individual steps marked a-g)Call for helpLook / listen / feelApply oxygen – faceApply oxygen – tracheostomyRemove any attachmentsAttempt suctionRemove tracheostomyTime to key interventions (measured in seconds for all individual steps below marked a-c)Apply oxygen to face and neckCall for helpCompletion of simulation

### Secondary Outcomes

Knowledge – multiple-choice question (MCQ) knowledge test – validated 10-question MCQ test, marked out of a total score of 23. This knowledge test will be based on the learning outcomes of the course and adapted from the National Tracheostomy Safety Project (NTSP) – E-Leaning for Healthcare modules [15]. These are well-established knowledge questions with electronic modules that thousands of participants have taken. The knowledge test will not be ‘validated’ for research purposes; however, it is certainly valid regarding face and content validity. The knowledge test will be administered four weeks following the intervention to measure retention.Participant satisfaction – Likert style questionnaire – Satisfaction questionnaire evaluating the use of VR for this education type and questions around the feasibility of doing this at home, unsupervised. Questions include a five-point Likert scale, true and false answers, and white space questions.Comfort and side effects – validated Virtual Reality Sickness Questionnaire [16]**—**this validated questionnaire assesses all possible VR sickness symptoms and will be delivered post intervention. The format of this questionnaire is a four-point Likert scale.Usability – validated System Usability Scale [17]**—**widely accepted questionnaire used to assess technology usability. The format of this questionnaire is a five-point Likert scale.

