To minimise the risk of cybersickness, teleportation was the preferred locomotion method for the user navigation within the VR environment [12]. Traditional VR movement options such as joystick-based locomotion can cause discomfort and disorientation due to mismatched sensory feedback. Teleportation on the other hand, allows the user to snap from one point to another reducing the likelihood of nausea and dizziness. Additionally, teleportation contributed to the performance of the simulation by keeping the frames per second (FPS) at a steady 72, which is a crucial factor when creating smooth and responsive experiences. Higher FPS ensures the virtual environment, interactive objects and animations are rendered smoothly, reducing lag that could negatively impact user experience and immersion.

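### The VR sickness score is taken post intervention only, with no pre-exposure score and no link to a home session, so it cannot separate VR effects from background symptoms and may miss or misrecall earlier ones

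*Protocol article*

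**What the plan says.** Comfort and side effects are a secondary outcome, measured with the Virtual Reality Sickness Questionnaire. Secondary Outcomes fixes its timing: "this validated questionnaire assesses all possible VR sickness symptoms and will be delivered post intervention". On the response format it adds only this: "The format of this questionnaire is a four-point Likert scale". It does not say whether the items ask about symptoms now or over the week.

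The exposure is set out under Description of the intervention. Participants receive a headset "which they will take for one week", and "The participants will be expected to use the application at least four times", with no upper limit. One run of the package takes around 20–35 min. At the first visit, "demographic data and the pre-course knowledge test will be administered", followed by a recorded simulation; no symptom score is mentioned. Use during the week is logged: "They will be required to record their use, and we will record how many times it has been used and for how long". Symptoms are not named as part of that log.

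At the end of the week the headset is returned and a second, non-VR simulation is done. The same section then says: "The participant will also complete the electronic post-course questionnaire with a repeat knowledge test". It does not name the sickness scale there.

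Materials and methods links cybersickness to movement inside the headset and gives this as the reason for the locomotion method: "Teleportation on the other hand, allows the user to snap from one point to another reducing the likelihood of nausea and dizziness".

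**The concern.** The article describes cybersickness as something that movement in VR provokes, so the natural unit of exposure is the session. The measurement is attached to no session. It comes after the whole intervention, which consists of several unsupervised sessions spread over a week. Nothing in the text limits the time between the last session and the questionnaire.

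The score also has nothing to be compared with. No symptom score is described before exposure, and no concurrent group without VR completes the scale. The historical controls attended a simulation course and offer no VR sickness comparator. Skills and knowledge are measured before and after the intervention; side effects are not.

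At stake is how far the study can report on the tolerability of unsupervised home use, and whether it can show that steps taken to limit cybersickness, such as teleportation, left few symptoms.

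**Working it through.** The plan states no figure on this point, so there is none to reproduce. The check sets the schedule against the measurement.

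**Inputs (all from the article)**

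| Item | Value | Section |
|---|---|---|
| Sickness scale, stated timing | post intervention; no other administration described | Secondary Outcomes |
| Recall period | not stated | Secondary Outcomes |
| Measures before exposure | demographics, knowledge test, recorded simulation | Description of the intervention |
| Home period | one week | Description of the intervention |
| Uses expected | at least 4 | Description of the intervention |
| Length of one run | around 20–35 min | Description of the intervention |
| Content of the use record | use, number of times, duration | Description of the intervention |
| Full list of data collection points | Appendix 1, not shown | Outcome measures |

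**Step 1: exposure covered by one score.** Assume that each use is a full run. Minimum headset time = number of uses × length of run: 4 × 20 = 80 min to 4 × 35 = 140 min, spread over up to 7 days.

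**Step 2: how near the score is to a session.** Suppose the form is completed immediately after the last of four uses. Then 4 − 1 = 3 sessions lie further back; with more uses, more do. If instead it is completed at the end of the week, the gap since the last session is uncontrolled. It can run from about 0 to about 7 days, depending on when the participant last used the headset.

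**Step 3: what the score captures, by recall period.**
- *Current symptoms:* symptoms from an earlier session count only if they persist to the time of the form. Those that have resolved are missed, so the score may understate session symptoms.
- *Symptoms over the week:* earlier symptoms can be reported, but from memory across at least four sessions. The problem is then recall error, and its direction is unknown.

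**Step 4: what the score can estimate.** Write the post-intervention score as S_post = b_post + v + e, where b_post is the background symptom level, v the part due to VR and e error. One score per person cannot separate b_post from v. With a score before exposure, S_pre = b_pre + e′, the difference is

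S_post − S_pre = v + (b_post − b_pre) + (e − e′).

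This estimates v if the background level is on average unchanged. Neither recall period in Step 3 supplies S_pre.

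**The case against.** The strongest reply is that this is a condensed article. It says that all data collection points are in Appendix 1, and that appendix is not shown. It may hold a recall period, a symptom field in the use record or a further administration. That limits how large the problem can be said to be. It does not remove it, because the article itself states when the scale is given and describes the first-visit measures and the log. If Appendix 1 schedules more, the text should say so.

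Other planned data would help. A participant who stops early would show in the logged number and length of uses, the satisfaction questionnaire has free-text items and covers feasibility at home, and a distress protocol exists. None of these is a symptom score before exposure or after a session.

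A reader might infer more than the documents support:
- *That symptoms will largely have passed by the time of the form, or that someone ill at first use is recorded as symptom-free.* The article gives no duration of symptoms and no recall period. A whole-week form could record early symptoms.
- *That the score is contaminated by the second simulation.* Placing the scale in the end-of-week post-course questionnaire is the natural reading, but it is not stated; nor is its order relative to the simulation.
- *That the score is biased towards no sickness overall.* Missed early symptoms would lower it and background symptoms would raise it, so the net direction is unknown.
- *That no symptom could ever be attributed to VR.* This is too absolute if items ask about symptoms due to VR, although self-attribution is not an estimate of change.
- *That the second research question depends on it.* That question concerns enjoyment and perceived learning, and sickness is not part of it.

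**Conclusion.** The point holds in a limited form. As described, the side-effect outcome is one post-intervention score for at least four home sessions, with no pre-exposure score and no stated link to a session. Within-person change cannot be estimated, and VR effects cannot be separated from background symptoms. Symptoms from earlier sessions may be understated (current-state form) or misrecalled (whole-week form). The size of this error cannot be computed from the article.

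The conclusion assumes that the text describes every administration of the scale; Appendix 1 could change that. The 80–140 min figure assumes full runs at the minimum number of uses. The consequence is confined to a secondary outcome with no stated hypothesis or threshold; the primary outcome and the non-inferiority comparison are untouched. The change is worth making because it is cheap, not because the study's main conclusion is at risk.

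**What to change.** 1. Give the same sickness questionnaire once at the first visit, before the headset is issued.
2. Give it electronically at home right after the first and the last VR session, or after each session, attached to the use record that participants already keep.
3. Report the change from the pre-exposure score to the post-session scores. Show how many home entries are missing, and set them beside the logged number of uses so that early stopping can be seen.
4. Keep the post-intervention administration for persisting symptoms. State its recall period and record the time since the last headset use.
5. If Appendix 1 already schedules any of this, bring the text of Secondary Outcomes into line with it.

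The cost is a short form completed a few more times, slight extra burden for participants and some missing home entries. The sample size, visits and primary analysis do not change.
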